#### Additional interventions

Necrosectomy will be considered in WON with predominantly solid debris, using the technique at the discretion of the endoscopist. In cases that require sessions of endoscopic necrosectomy, the different technical variants described in the literature will be used (irrigation technique with normal saline; mechanical technique using the common devices as snares, Dormia baskets or retrieval nets for extraction of necrotic debris; or combined with nasocystic catheters). The periodicity will be every 2–5 days depending on the decision of the expert endoscopist and the clinical evolution of the patient.

#### Additional comments

In the event of technical failure in the placement of the stent (plastic or LAMS) for any reason, alternative treatment will be decided upon in accordance with the directives of the endoscopic interventionist, with the aim of offering the patient the best possible solution.

The first controls will be on the first day following and at 4 weeks (see Table 4). If there is no short-term clinical success, the most beneficial therapeutic approach for the patient will be adopted in accordance with the criteria of the patient’s medical team (for example: the use of technical variants at initial drainage such as placement of coaxial plastic pigtail within the LAMS, replacement or change the stent type, use of nasocystic drainage or other known variants).

**Table 4 Tab4:** Data management, calendar

Timepoint/stages	Study Period									
	Baseline	Intervention	24 h	7 days ±	4 weeks ± 3 days	8 weeks ± 5 days (Telephone)	16 weeks (4 months) ± 10 days	6 months ± 10 days (Telephone)	8 months ± 10 days	12 months ± 10 days (Telephone)
Enrollment										
Informed consent	X									
Clinical history and exploration	X									
Eligibility screen	X									
Allocation	X									
Intervention										
Implantation		X								
Removal					X					
INR		X								
Assessments:										
Blood test	X		X		X		X		X	
Imaging test	X	X			X	X^a^	X		X	
Symptomatology	X		X	X	X	X	X	X	X	X
Visit			X		X		X		X	
Telephone contact				X		X		X		X
Adverse effects	X	X	X	X	X	X	X	X	X	X
Primary outcome					X					
Secondary outcomes					X					
Medication	X	X	X	X	X	X	X	X	X	X

^a^Only in case of radiological clinical success but with persistence of the collection > 5 cm

Every intervention, diagnostic procedure, and additional therapeutic contribution will be noted in the CRF.

In the case of collections of significant size (i.e., 14 cm) with clinical-radiological success but without the disappearance of the collection (i.e., CTMD reduction from 14 to 6 cm), precluding the removal of the stent, a new CTMD will be performed at 4 weeks (8 weeks) to assess removal of the stent.

Therefore, the removal of a stent is contemplated when there is disappearance of the collection or a decrease < 5 cm.

Patients will remain in the hospital for a minimum of 24 h for clinical observation, under medical supervision.

### Clinical evaluation and follow-up

#### Data collection

The collecting of clinical information on the patients will begin at the outset (baseline) and will continue with follow-up as established and defined in the study. AEs will be noted from the beginning of the test until the conclusion of follow-up by means of scheduled controls.

#### Calendar

The following time-points and data items will constitute the data collection from the beginning through successive controls: The collecting of data for purposes of documentation will be carried out using a CRF, which will serve as an easily accessed source of information. After collection, the data will be introduced into an electronic database by the participating investigator of each center.

#### Follow-up

Patients will be assessed (visit, telephone call) on days 1 and 7, at 4, 8, and 16 weeks, and at 6, 8, and 12 months by personnel participating in the study, with the aim of obtaining information regarding signs and symptoms pointing to possible stent obstruction or migration, recurrence, or other AEs.

Any instances of death during the follow-up will be investigated to rule out any possible relation to the endoscopic procedure. Such occurrences will also be recorded in the CRF.

If there is clinical suspicion of obstruction or migration of the stent, an upper endoscopy will be carried out. Based on the findings of this procedure, the problem will be resolved in accordance with the directives of the intervening endoscopist. Any additional procedure or endoscopic intervention will be duly documented.

Complications will be handled and treated in accordance with the directives of the patient’s medical team. All additional tests and interventions will be duly documented.

### Definitions

The term WON is in accordance with the literature (latest revision of Atlanta, Banks PA et al. Gut 2013) [1]. At least two imaging tests will be required (CTMD, MRI, EUS) prior to the transmural drainage, the results of which must be in agreement on the classification of the collection as WON.

Technical success is defined as the correct release of the stent at both ends, with observed drainage of the liquid.

Clinical success is defined as the significant reduction of the collection along with clinical resolution.

Recurrence is defined as a symptomatic pancreatic collection diagnosed with imaging test during the follow-up of prior procedure with initial clinical success.

AEs are defined as undesirable situations suffered by patients during the study, whether related or not to the EUS-guided transmural drainage with a stent (plastic or metal). All AEs referred by patients or observed by the medical team will be duly documented. All serious AEs will be detailed, and the study promoter/principal investigator will be notified within 7 days. In the event of a death, notification will be made within 24 h. AEs will be recorded in both the clinical history of the patient and the CRF, with appropriate medical terminology. Whenever possible, the diagnosis rather than the symptoms will be recorded. These guidelines are to be followed from the time of the signing of informed consent until 30 days after the final visit in the study calendar. AEs will be classified as mild, moderate, serious, or fatal, in accordance with the nomenclature for AEs in endoscopy (ASGE Workshops 2010, Cotton GIE 2010; 71:446–54). The determination as to whether an AE is related to the EUS-guided transmural drainage with stent (plastic or metal) will be made by the patient’s medical team, the local investigator, and the principal investigator of the study.

In Additional file 2 is included information about AE definitions and MEDDEV guidelines. “Research product security surveillance” section, according to the definitions set out in the MEDDEV 2.7/3 guidelines (rev 3, May 2015) “Guidelines on medical devices: Clinical investigations: Serious adverse event reporting under Directives 90/385/EECC and 93/42/EEC” (Additional file 2).

### Outcomes

The primary outcome is the short-term (4 weeks) clinical success (metal vs. plastic) determined by the reduction of the collection (to < 50% or < 5 cm in size), along with clinical improvement.

The secondary outcomes are long-term (4 months) clinical success (metal vs. plastic) determined by total resolution or 5 cm, along with clinical improvement. Technical: to assess the duration of the procedure and the level of difficulty. Safety: to assess AE (early and late). Hospital length of stay. Recurrences. Financial: evaluate the relative costs of the two strategies.

### Sample-size calculation

The sample-size calculation is based on the primary hypothesis of detecting statistically significant differences in the percentage of clinical success in the LAMS and plastic-stents groups at 4 weeks after the intervention. Published data suggest that the clinical success rate at 4 weeks in the LAMS group is expected to be 0.75 and in the plastic-stent group it is expected to be 0.5. Fifty-seven patients will be recruited in each group to reject the null hypothesis that the proportion of clinical success in the LAMS group is equal to that of the plastic group with an 80% power. The type-I error associated with this test will be 5%. To evaluate the hypothesis, the chi-square test or Fisher’s exact test will be used depending on of the application criteria. For the calculation, a planned interim analysis will be made for half of the recruitment using O’Brien-Fleming’s type-I error expense function and a global loss rate of 5%. http://www.stat.ubc.ca/~rollin/stats/ssize/b2.html

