### Statistical analysis

All study variables will be presented for stent groups and in total, using descriptive statistics consistent with the nature of the variable. The continuous variables will be described indicating the number of non-missing observations, the mean, the standard deviation, the minimum, the first quartile, the median, the third quartile, and the maximum. Categorical variables will be described indicating the number of non-missing observations and the percentages of the different categories by column.

Main analysis: main outcome is the percentage of patients’ radiological (morphological) success between transmural drainage of the collection, measured at 4 weeks from intervention. The null hypothesis suggests that there are no differences between the proportions of the intervention group and the control group.

The level of statistical significance has been set at 5%. To test the hypothesis, use the chi-square test or Fisher’s exact test depending on the application criteria will be used. To quantify the magnitude of the difference, the relative risk of success will be estimated, in the metal-stent group with respect to the plastic-stent group and its confidence interval will be calculated at 95%.

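### After the stated 5% loss, 57 recruited per group give about 78% power for the named chi-square test (77–79% by formula), not the stated 80%

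*Protocol article*

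**What the plan says.** The Sample-size calculation section assumes that "the clinical success rate at 4 weeks in the LAMS group is expected to be 0.75" and that "in the plastic-stent group it is expected to be 0.5". It then states: "Fifty-seven patients will be recruited in each group to reject the null hypothesis" that the LAMS proportion is "equal to that of the plastic group with an 80% power". The error rate follows: "The type-I error associated with this test will be 5" per cent. The test is chi-square or Fisher's exact, chosen by the usual criteria for applying them. The same paragraph says that the calculation allows for one interim analysis at half of recruitment, using the O'Brien-Fleming "type-I error expense function and a global loss rate of 5" per cent.

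The Statistical analysis section gives the null for the main analysis: "The null hypothesis suggests that there are no differences between the proportions of the intervention group and the control group". It adds "The level of statistical significance has been set at 5" per cent and asks for a 95% confidence interval for the relative risk. Neither section names the variance formula or says whether the test is one- or two-sided.

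**The concern.** The paragraph presents 57 as a recruitment figure that already carries two inflations, one for loss and one for the interim look. A fixed-sample chi-square calculation with no loss and no look lands at almost the same number. If so, the inflations are named but not applied. The trial would then have less power than stated for its primary comparison, and readers would take the 80% at face value when interpreting a non-significant result.

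**Working it through.** **Inputs.** From the Sample-size calculation section: p1 = 0.75, p2 = 0.50, type I error 0.05, power 0.80, 57 recruited per group, 5% loss, one look at half of recruitment with O'Brien-Fleming spending. From Methods/design: 1:1 allocation. Assumed: two-sided testing, because the null in the Statistical analysis section is one of no difference. Normal quantiles: 1.960 and 0.8416.

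**Trying to reproduce 57.**

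- *Pooled variance, matching the chi-square test.* The mean proportion is 0.625, so n = [1.960·√(2·0.625·0.375) + 0.8416·√(0.1875 + 0.25)]² / 0.25² = [1.3419 + 0.5567]² / 0.0625 = 57.7, so 58. With loss: 57.7/0.95 = 60.7, so 61. With loss and look: 61.0 (Lan-DeMets boundaries) to 61.2 (classical O'Brien-Fleming), so 61 to 62.
- *Unpooled variance.* n = (1.960 + 0.8416)² · 0.4375 / 0.0625 = 54.9, so 55. With loss: 54.9/0.95 = 57.8, so 58. With loss and look: 58.0 to 58.3, so 59 after rounding up.
- *Arcsine.* 57.3 before loss, 60.3 after.
- *One-sided 5% with continuity correction.* 54 before loss; 54/0.95 = 56.8, so exactly 57. This omits the look and does not fit a no-difference null.

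The stated 57 is thus close to the pooled or arcsine figure with nothing added, or one to two patients short of the unpooled figure with both adjustments. None of the two-sided formulas tried gives 57 or fewer with loss and look included.

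**Power of what is planned.** Evaluable per group: 57 × 0.95 = 54.15, taken as 54.

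- Pooled: Φ[(0.25·√54 − 1.960·√0.46875)/√0.4375] = Φ[(1.8371 − 1.3419)/0.6614] = Φ(0.749) = 77.3%.
- Unpooled: Φ[1.8371/0.6614 − 1.960] = Φ(0.817) = 79.3%.
- Exact binomial enumeration of the uncorrected chi-square test: 77.9%.
- For comparison, 57 evaluable with no loss at all: 79.5% pooled, 79.8% exact.

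**Effect of the look.** At half information the Lan-DeMets O'Brien-Fleming boundaries are Z = 2.963 (p = 0.0031) and Z = 1.969 (p = 0.0490). The classical ones are 2.797 and 1.977 (final p = 0.0480).

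| 54 evaluable per group | No look | Lan-DeMets | Classical |
|---|---|---|---|
| Pooled | 77.3% | 77.1% | 76.9% |
| Unpooled | 79.3% | 79.2% | 79.0% |

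By these approximations the look costs 0.1 to 0.4 points. Exact enumeration with the Lan-DeMets look gives 78.0%. The loss costs 79.5 − 77.3 = 2.2 points on the pooled formula.

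**The case against.** The strongest reply is that 57 is not a demonstrable arithmetic error. The article names neither formula nor sidedness, and it points to an online calculator that is not part of the documents. A standard unpooled calculation with both adjustments comes within one or two patients of 57 and leaves power at 79.0–79.2%. That stands, and it is why the conclusion is a range. It does not restore 80%: the unpooled result is still above 57, and exact enumeration, which needs no variance formula, puts the named test at about 78%, nearer the pooled value.

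Sidedness matters more. At a one-sided 5% level, 54 evaluable per group would give 85.9% by the pooled formula. The no-difference null makes that reading unlikely, but the text does not exclude it.

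Two stronger readings are tempting and should not be drawn.

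- A reader might infer that the final test spends the full 5% after the look, so that the type I error is not held. The documents do not say this. The sample-size section specifies O'Brien-Fleming spending with 5% error, and the 5% in the Statistical analysis section can be read as the overall level. The nominal final level is also commonly left to the analysis plan. Even a final test taken literally at 0.05 would give an overall error of only 5.1% (Lan-DeMets) to 5.2% (classical).
- A reader might infer a much larger loss of power because Fisher's test is mentioned. Under the planning rates the smallest expected cell is about 54 × 0.375 = 20, so the usual criteria select chi-square.

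**Conclusion.** The point holds in a limited form. With the 5% loss that the paragraph says is included, 57 recruited per group deliver about 78% power for the uncorrected chi-square test, with a range of 77–79% by formula. The 57 is essentially the chi-square requirement before inflation; 61 to 62 per group would match the stated 80% on that formula. The gap is one to three points and comes almost wholly from the loss. The conclusion rests on two-sided testing at 5%, the protocol's own success rates, loss falling equally on both groups, and a look at half of the information.

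**What to change.** In the Sample-size calculation section, keep 114 patients and restate power as about 78% (77–79% depending on the formula) with 54 evaluable per group after 5% loss. State the variance formula and that the test is two-sided, or give the sidedness actually used.

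As a minor clarification in the Statistical analysis section, say that 5% is the overall two-sided level and that the final test and its interval use the O'Brien-Fleming spending boundary at the actual information fraction. That is about 0.049 if the look falls at half.

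The cost is wording only: no added patients, visits or procedures, and a stated power slightly less favourable than the present one.

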### Statistical analysis

All study variables will be presented for stent groups and in total, using descriptive statistics consistent with the nature of the variable. The continuous variables will be described indicating the number of non-missing observations, the mean, the standard deviation, the minimum, the first quartile, the median, the third quartile, and the maximum. Categorical variables will be described indicating the number of non-missing observations and the percentages of the different categories by column.

Main analysis: main outcome is the percentage of patients’ radiological (morphological) success between transmural drainage of the collection, measured at 4 weeks from intervention. The null hypothesis suggests that there are no differences between the proportions of the intervention group and the control group.

The level of statistical significance has been set at 5%. To test the hypothesis, use the chi-square test or Fisher’s exact test depending on the application criteria will be used. To quantify the magnitude of the difference, the relative risk of success will be estimated, in the metal-stent group with respect to the plastic-stent group and its confidence interval will be calculated at 95%.

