#### Secondary variable analyses

To determine which factors are associated with clinical-radiological success in the short term, a multivariate logistic regression will be carried out. The variables of age and sex, and factors predicting the location of the disease, treatments received, size, and characteristics of the collection, previous ASA, etc. will be taken. In addition, the appearance of clinical recurrence will be considered by means of an analysis of Kaplan-Meier survival. The factors associated with clinical recurrence will be explored through a multivariate Cox proportional risk model and adjustment variables will also be taken.

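### The main-analysis text names 4-week radiological success as the main outcome, while the declared primary outcome and the sample size are for clinical success (size criterion plus clinical improvement)

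*Protocol article*

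**What the plan says.** All places are in the protocol article.

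- **Outcomes** (and the Abstract, in the same sense): the primary outcome is short-term (4 weeks) clinical success, "determined by the reduction of the collection (to < 50% or < 5 cm in size), along with clinical improvement".
- **Sample-size calculation**: the primary hypothesis concerns "detecting statistically significant differences in the percentage of clinical success in the LAMS and plastic-stents groups at 4 weeks after the intervention". The expected rates are 0.75 (LAMS) and 0.5 (plastic), with 57 patients per group, 80% power and 5% type-I error. An interim analysis is planned at half of recruitment.
- **Statistical analysis**, main analysis: the main outcome is the percentage of patients with "radiological (morphological) success between transmural drainage of the collection", at 4 weeks. The null hypothesis, the chi-square or Fisher test and the relative risk with its 95% interval follow from that sentence. No clinical component is named.
- **Secondary variable analyses**: the regression is introduced with "To determine which factors are associated with clinical-radiological success in the short term". The same compound term appears under Additional comments.
- **Definitions**: "Clinical success is defined as the significant reduction of the collection along with clinical resolution".
- **Statistical analysis plan**: the plan is to be final before the database closes and will contain the analyses described in the article. A departure in the analysis of the main variable calls for a protocol addendum, and nothing may change after closure.

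**The concern.** The section that lays out the confirmatory analysis names a variable that is not the declared primary outcome. The two differ for one kind of patient: size criterion met, no clinical improvement. That patient is a success in the main-analysis text and a failure under Outcomes.

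Three things follow if the text is left as it stands. The planning rates are labelled clinical success, so the power statement has no stated basis for radiological success. The ASA subgroup section repeats the main analysis, so it inherits the ambiguity. And in a trial without masking and with an interim look, an unsettled primary variable leaves room to choose between two readings after data have been seen.

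**Working it through.** **1. Are these two terms for one thing?** The main-analysis sentence narrows *radiological* with *morphological* in parentheses, which points to imaging alone. The article has a separate compound term for the combined endpoint, used in the regression section and under Additional comments. Read literally, the confirmatory test uses imaging alone and the secondary regression uses the composite.

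**2. Reproduce the plan's figure for clinical success.** Inputs from Sample-size calculation: p1 = 0.75, p2 = 0.50, 5% error, 80% power. Two-sided testing is assumed, because the null is equality of proportions. With the mean rate p̄ = 0.625 and the pooled normal approximation:

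n per arm = [1.960 × √(2 × 0.625 × 0.375) + 0.842 × √(0.75 × 0.25 + 0.50 × 0.50)]² / 0.25² = (1.342 + 0.557)² / 0.0625 = 57.7, so 58.

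This is within one patient of 57, before any allowance for loss. Power at 57 per arm:

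Φ[(0.25 × √57 − 1.342) / 0.661] = Φ(0.825) = 79.5%.

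With the planned 5% loss (57 × 0.95 ≈ 54 per arm), power is 77.3%. The interim look is ignored here. The stated size therefore fits the clinical-success rates.

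**3. What carries over to radiological success?** Assume that radiological success means the size criterion of the Outcomes section. Every composite success is then also a radiological success. In each arm let d be the share of patients who meet the size criterion without clinical improvement. Then:

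- radiological rate = composite rate + d
- radiological difference = 0.25 + (d in LAMS − d in plastic)

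The article gives neither d nor a radiological rate. The difference can stay the same, shrink or grow.

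**4. Illustrations only.** The values of d are assumed; 57 per arm, same power formula as in step 2.

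| d, LAMS / plastic | Radiological rates | Difference | Power |
|---|---|---|---|
| 0 / 0 | 0.75 v 0.50 | 0.25 | 79.5% |
| 0.15 / 0.15 | 0.90 v 0.65 | 0.25 | 90% |
| 0.10 / 0.10 | 0.85 v 0.60 | 0.25 | 85.8% |
| 0.10 / 0.15 | 0.85 v 0.65 | 0.20 | 70% |
| 0.10 / 0.20 | 0.85 v 0.70 | 0.15 | 48% |
| 0 / 0.10 | 0.75 v 0.60 | 0.15 | 40.0% |
| 0.15 / 0.30 | 0.90 v 0.80 | 0.10 | 32% |

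For example, for 0.75 v 0.60 with p̄ = 0.675: Φ[(0.15 × √57 − 1.960 × √(2 × 0.675 × 0.325)) / √(0.1875 + 0.24)] = Φ[(1.132 − 1.298) / 0.654] = Φ(−0.254) = 40.0%.

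The spread reflects the chosen inputs. It shows that the 80% cannot be carried over; it does not estimate the actual power.

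**The case against.** **Loose drafting.** The Abstract, Outcomes and Sample-size calculation agree on clinical success. The sample-size section itself attaches the chi-square or Fisher test to that endpoint at the same time point. The main-analysis sentence is visibly garbled, and a Table 4 footnote mixes the terms too. This stands in part: a reader might infer that the sponsor means to test a different endpoint, and the article does not show that. The conflict remains all the same, because this is the section that sets out the main analysis and its effect measure, and it names the other variable.

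**The analysis-plan safeguards.** Finalising the plan before database closure, with an addendum for departures on the main variable, limits a choice after the fact. It does not settle the matter. The article does not say which section governs, so it is unclear which choice would be a departure. The plan is due only by database closure, whereas the interim analysis comes at half of recruitment.

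**A third primary variable.** A reader might count Definitions as another rival endpoint, since it requires *resolution* where Outcomes requires *improvement*. It is a general definition with no time point and no size threshold, so it is not a competing analysis variable. The difference still matters for one patient group: someone who has improved but still has symptoms can be a success under Outcomes and fails only under Definitions.

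**The planning rates.** They rest on published data that are not shown, so how success was defined there is unknown. What can be said is that the article labels them clinical success.

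**Conclusion.** The point holds as a contradiction in the current text: the main analysis is written for 4-week radiological success, while the declared primary outcome and the sample size are for clinical success. It must be settled, because it concerns the variable of the confirmatory test.

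Its effect on the result cannot be sized from the article. The 80% power is supported for clinical success only (79.5% recomputed, two-sided, normal approximation). For radiological success it is unknown. A reader might take the lower illustrative figures as evidence that the trial is underpowered; they are not, since they depend on assumed rates and other equally admissible rates give more than 80%.

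**What to change.** - In **Statistical analysis**, name the Outcomes composite as the main-analysis outcome: size criterion AND clinical improvement at 4 weeks, yes or no for each patient. Apply the null hypothesis, the test and the relative risk to it.
- Report radiological success as a named secondary or component outcome.
- Use one wording for the clinical component in **Definitions** and **Outcomes**, and make sure that the full protocol or the analysis plan turns it into a yes/no rule.
- Make the change by dated addendum before the interim analysis. The article does not say whether that analysis has taken place. If it has, make the change before database closure and state what was known at the time.

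The cost is an amendment of wording. Table 4 already schedules imaging and symptoms at 4 weeks, so no new data are needed. The sample size needs no change for this point, because the planning rates are stated for clinical success.

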### Study population

This clinical trial will be performed at the endoscopy unit of the digestive diseases departments of nine tertiary and university centers in Spain. In order to participate in this study, the patient must be a candidate for guided transmural drainage with EUS of WON-type pancreatic collection as a local complication in acute pancreatitis. The investigator at each center will be contacted to evaluate the inclusion of the patient in the study. The patient will be correctly informed by personnel knowledgeable about the specifics of the study, who will help to resolve any questions that may arise. The informed consent form will be signed in the presence of participating personnel knowledgeable about the study. The patient has the right to opt out of the study at any time.

The inclusion and exclusion criteria are listed in Table 2.

**Table 2 Tab2:** Selection criteria for WON walled-off necrosis. ^a^Diagnosis of WON based on imaging procedures

Inclusion criteria:	
*Patients eligible for the trial must comply with all of the following at randomization* • Age 18 years or older • Patient with indication (ASGE, Jacobson BC, GIE2005) of drainage of only one type^a^ related to the symptomatology, as a local complication of previous acute pancreatitis • Patient capable of understanding and signing informed consent form • Patient understanding the type of study and complying with the follow-up of complementary tests during the study’s duration	
Exclusion criteria	
• Pregnancy or breast-feeding • Severe coagulation disorder: INR > 1.5 not correctible with administration of plasma and/or platelets < 50,000/mm^3^ • Asymptomatic patients, without clinical indication of drainage, except for those with vascular compression involvement • Non-identification of solid content during EUS procedure • Failure to sign informed consent form • Patients with intellectual handicap who are unable to understand the nature and possible consequences of the study, unless there is a competent legal representative • Patients unable to adhere to subsequent follow-up requirements • Conditions that preclude upper digestive endoscopy, such as stenosis	

*Note*: If there are several pancreatic collections, this does not exclude the patient from the trial. The patient is only excluded if there is more than one symptomatic collection to be drained

*EUS* endoscopic ultrasound, *INR* international normalized ratio

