### Randomization and masking

Patients will be enrolled in this trial by gastroenterologists, surgeons, and endoscopists who will evaluate the cases in the inpatient wards or in the outpatient consultation areas. The participants will be randomized with a random-number table generated by an online platform.

A code list will be generated by randomization with a 1:1 randomization ratio, by blocks, stratified by centers and by American Society of Anesthesiologists’ classification (ASA) score. Each individual will be assigned a randomization code along with the treatment that corresponds. Once the patient meets the eligibility criteria and has provided informed consent, we will proceed to the allocation of each participant centrally, ensuring allocation concealment, and based on the randomization list. To prevent different subject recruitment rates at the various hospitals from interfering with the development of the study, the entire population will be randomized in blocks of four between the two treatment possibilities.

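### Randomisation is stratified by centre and ASA class, but the primary test and relative risk ignore both, which makes them conservative if those factors are materially prognostic

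*Protocol article*

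**What the plan says.** Under Randomization and masking, allocation is "by blocks, stratified by centers and by American Society of Anesthesiologists" score. The same section then says that "the entire population will be randomized in blocks of four between the two treatment possibilities".

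The Sample-size calculation and Statistical analysis sections both name a chi-square or Fisher's exact test for the primary outcome; the latter reads "To test the hypothesis, use the chi-square test". The effect measure follows: "the relative risk of success will be estimated, in the metal-stent group with respect to the plastic-stent group", with a 95% confidence interval. Neither section mentions centre or ASA.

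ASA returns in two places: as a covariate in the logistic regression of factors associated with success (Secondary variable analyses), and as the one subgroup factor (Subgroup analysis). Centre appears in no analysis.

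The section headed Statistical analysis plan says that the later plan will contain the analyses already described plus others, and that a deviation in the analysis of the main variable calls for a protocol addendum. The unstratified primary analysis is therefore fixed in this document and not left open.

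**The concern.** Stratified blocking balances the arms within each centre-by-ASA cell. If success differs between cells, that balance removes the between-cell variation from the treatment comparison. A crude chi-square test and a crude relative-risk interval still count that variation as noise. Their standard error is then too large, the test rejects less often than its nominal 5%, and the interval is wider than it needs to be.

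At stake is precision that the design has already arranged for at no cost in patients. Both factors are known at randomisation, so using them in the analysis needs no new data.

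**Working it through.** **Inputs from the protocol article.** Success rates 0.75 (LAMS) and 0.50 (plastic), 57 patients per group, "equal to that of the plastic group with an 80% power", and "The type-I error associated with this test will be 5" percent (Sample-size calculation; sidedness is not stated, two-sided assumed). Block size four. Centres: "nine tertiary and university centers in Spain".

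**Inputs assumed.** The documents do not say how many ASA levels define the strata, nor how strongly centre or ASA predicts success. The ranges used are two or four ASA levels, centre SD 0 to 1 on the log-odds scale, and ASA odds ratio (OR) 1 to 9 between extreme classes.

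**Step 1: reproduce the stated size.** Unstratified two-proportion formula, pooled variance, no continuity correction:

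n = [1.96·√(2·0.625·0.375) + 0.8416·√(0.75·0.25 + 0.5·0.5)]² / 0.25² = (1.342 + 0.557)² / 0.0625 ≈ 57.7, so 58 per group.

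The arcsine version gives 57.3, and power at 57 per group is 79.5%. The stated 57 is thus close to a calculation for the same unstratified test that the analysis names.

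**Step 2: mechanism.** With success probability p_k in cell k, the crude test uses variance p̄(1−p̄) = E[p_k(1−p_k)] + Var(p_k). Under balance within cells, only the first term drives the difference between arms. The excess Var(p_k) is zero if the strata are not prognostic, and it is never negative.

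**Step 3: simulation.** 114 evaluable patients, nine centres, two ASA levels (18 cells), permuted blocks of four within cells, no interim look, 4000 runs. Monte Carlo error is about 0.3–0.4 points on type-I error and 0.6–0.7 points on power. CMH is the Cochran-Mantel-Haenszel test over all 18 cells.

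| Centre SD, ASA OR | Type-I, crude | Type-I, CMH | Power, crude | Power, CMH | Difference in power |
|---|---|---|---|---|---|
| 0, 1 | 4.9% | 4.6% | 79.6% | 78.6% | −1.0 |
| 0.3, 1.5 | 5.0% | 4.9% | 81.5% | 80.4% | −1.1 |
| 0.5, 2 | 4.4% | 5.1% | 80.6% | 82.4% | +1.8 |
| 0.5, 4 | 4.0% | 5.2% | 82.0% | 84.5% | +2.5 |
| 1, 4 | 3.3% | 5.4% | 82.8% | 87.5% | +4.7 |
| 1, 9 | 2.4% | 4.8% | 83.2% | 90.3% | +7.1 |

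A separate simulation gave crude type-I errors of 4.2% (SD 0.5, OR 2), 3.3% (SD 0.5, OR 4) and 2.8% (SD 1, OR 4). In it, a CMH test by two-level ASA with the centres pooled into three groups gained about 1, 3 and 2 points of power in those settings. It lost at most about 0.5 point when the strata were not prognostic.

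**Step 4: the interval.** With the nine centre effects held fixed, the crude 95% relative-risk interval covered the design value of 1.5 as follows: 95.0% (not prognostic), 96.2% (SD 0.5, OR 2), 97.0% (SD 1, OR 4) and 97.4% (SD 1, OR 9). A hand check compares the mean reported standard error of the log relative risk with its actual spread. For SD 1, OR 4 these are 0.155 and 0.142, so expected coverage is 2Φ(1.96·0.155/0.142) − 1 = 2Φ(2.14) − 1 ≈ 96.8%. For SD 0.5, OR 2 they are 0.155 and 0.151, which gives about 95.6%.

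**Step 5: sparse cells.** Four ASA levels make 36 cells, or 114/36 ≈ 3.2 patients per cell. CMH over every cell then has 72.7% power against 79.0% for the crude test when the strata are not prognostic, 76.2% against 79.7% at SD 0.5, OR 2, and 82.9% against 82.0% at SD 1, OR 4. In that setting, stratifying by ASA alone or by centre alone stays between about 1 point below and 3 points above the crude test.

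**The case against.** The strongest reply is that nothing here is invalid. Sample size and analysis use the same unstratified test, so the planned power is roughly what the planned test delivers, and the error can only be conservative. That stands: what is forgone is an extra gain.

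Second, a reader might infer that ignoring the strata necessarily wastes power and makes the test conservative. The documents do not support that. They give no prognostic strength for centre or ASA, and with absent or weak effects the crude test keeps its 5% and is level or about 1 point ahead. That the protocol uses ASA as stratifier, covariate and subgroup factor shows that its authors think ASA relevant, but gives no size.

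Third, a reader might infer that this choice pulls the trial below 80% power. It does not: simulated crude power is about 80–83% with all 114 patients evaluable. Any shortfall from the 5% loss or the interim look is a separate matter.

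Fourth, ASA does enter the secondary regression and the subgroup analysis. True, but neither is the primary comparison, and centre enters nowhere.

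Fifth, the sentence on randomising the whole population in blocks of four could mean one unstratified list. The crude test would then keep its size (simulated 4.8% at SD 1, OR 4), though adjustment would still add about 2 points of power (80.7% against 82.7%). Stratification is the explicit statement, so the point stands, but the ambiguity is real.

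**Conclusion.** The mismatch is in the text and is fixed there; its consequence is conditional. If centre or ASA is materially prognostic, which is an assumption, the crude test and interval are conservative. Type-I error is about 4.2–4.4% at moderate strength (SD 0.5, OR 2), between 3.3% and 4.0% at SD 0.5, OR 4, and about 2.4–3.3% at SD 1 with OR 4 to 9. For the nine centres taken as given, the interval covers about 96–97%.

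Roughly 1–2 points of power are forgone at moderate strength and 3–7 at strong. The upper end needs full stratification on two ASA levels with very strong effects; pooling centres into three groups recovered about 1 to 3 points.

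This is an efficiency loss. It does not bias the estimate or inflate false positives. It is worth correcting because the correction is cheap, not because the crude result would mislead.

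**What to change.** Issue the addendum that the protocol provides for, before any interim or final comparison between arms:

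- Primary test: Cochran-Mantel-Haenszel, stratified by ASA in two non-overlapping levels. The present subgroup split, I–II against II–IV, puts class II on both sides and must be settled first.
- Centre: include it only after pooling by a rule written down in advance. Do not use every centre-by-ASA cell.
- Estimate: the Mantel-Haenszel relative risk with its 95% confidence interval, over the same strata as the test.
- Interim: use the same test at the planned look at half recruitment.
- Sensitivity analysis: keep the crude chi-square or Fisher test and the crude relative risk.
- State whether the blocks of four run within centre-by-ASA strata or on one list, and how many ASA levels the list uses.

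The cost is the addendum itself and at most about 1 point of power if the strata prove not to be prognostic. It needs no extra patients or data, since both factors are recorded at randomisation.
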